## **CONFIDENTIAL**

the study. Any infant with antibody titres to EPI vaccines below the level of protection will receive a booster dose of that particular vaccine.

### **3 OBJECTIVES**

Primary:

- Safety and immunogenicity of MVA.HIVA vaccine in 20 week old healthy Gambian infants born to HIV-1/2-uninfected mothers.

Secondary:

- Gross impact of MVA.HIVA on the immunogenicity of EPI vaccines (DTwPHib, HepB, PCV-7 and OPV) when administered 4 weeks after the last EPI in infants who received BCG vaccine within the first two weeks of life. The trial will not be powered to detect small interference effects.

#### **Endpoints:**

For safety and reactogenicity: Actively and passively collected data on adverse events (AEs).

For immunogenicity to EPI vaccines: Antibody levels to specific vaccines.

For immunogenicity to MVA.HIVA: Frequency of IFN- $\gamma$  producing cells determined in ex-vivo (effector) and 10-day cultured (memory) ELISPOT assays after overnight stimulation with pools of HIVA-derived peptides. We shall consider the MVA.HIVA vaccine to be immunogenic in infants if at least 50% of vaccinees have detectable HIV-1-specific T cell responses at any time point after the vaccination. In the cultured IFN- $\gamma$  ELISPOT assay, a positive response is defined to be at least 250 SFU/10^6 cells above the no-peptide background, and at least 4x the no-peptide background. We shall be using standardized and trial-tested assays, which have been described in Goonetilleke et al. [48]. MVA.HIVA alone is not considered to be a strong priming vaccine, but it can strongly and consistently boost HIV-1-specific T cell responses if they have been previously primed [20, 21, 47, 48]. It is planned in the future to use the MVA.HIVA vaccine as a booster to a BCG.HIVA prime, which should enhance the generation of HIV-specific T cell levels after the MVA.HIVA vaccination.

### **4 STUDY DESIGN**

This is an open randomized phase I study evaluating the safety and immunogenicity of a single dose of MVA.HIVA vaccine administered at 20 weeks of age to infants born to HIV-1/2-uninfected mothers, and its gross impact on the immunogenicity of EPI vaccines administered not less than 4 weeks before. The immunology laboratory staff will be blinded for the study product / control group allocation.

**Study site:** Sukuta Health Centre, The Gambia

**CONFIDENTIAL****4.1 Sample size:**

A total of 48 mother-infant couples will be enrolled into the study and randomized in two groups of 24.

**Group 1:** MVA.HIVA administered at 20 weeks of age (n=24)

**Group 2:** Normal EPI vaccine schedule (control group) (n=24)

This study is a pilot study and the immunogenicity analyses will be mainly descriptive. As such, it is not powered to provide definitive evidence of vaccine-induced effects; rather it is based on smaller numbers of participants and will only indicate trends, feasibility, or size of effect and variability of measurements to inform the design of more definitive studies. The rate of serious adverse events will be used as one measure of the safety of the candidate vaccine. Table 2 shows examples of sample size calculations for safety in terms of the ability to detect SAEs, i.e. the probabilities of observing 0, 1+ (1 or more), 2+ or 3+ SAEs among group of n=24 for a range of possible true event rates. If none of the 24 volunteers receiving the vaccine experiences an SAE definitely related to the vaccine, the 95% two-sided upper confidence bound for the rate of such reactions in the population is 13.8% (Table 3).

**Table 2.** Probabilities of detecting events for n=24

| Event rate (SAE) | Detect. Probability (0 events/24 vol's) | Detect. Probability (1+ events/24 vol's) | Detect. Probability (2+ events/24 vol's) | Detect. Probability (3+ events/24 vol's) |
|------------------|-----------------------------------------|------------------------------------------|------------------------------------------|------------------------------------------|
| 0.010            | 0.88                                    | 0.11                                     | 0.01                                     | <0.01                                    |
| 0.025            | 0.74                                    | 0.26                                     | 0.03                                     | <0.01                                    |
| 0.035            | 0.65                                    | 0.35                                     | 0.06                                     | 0.01                                     |
| 0.050            | 0.54                                    | 0.46                                     | 0.12                                     | 0.02                                     |
| 0.100            | 0.28                                    | 0.72                                     | 0.34                                     | 0.11                                     |
| 0.150            | 0.14                                    | 0.86                                     | 0.56                                     | 0.26                                     |
| 0.200            | 0.07                                    | 0.93                                     | 0.73                                     | 0.44                                     |
| 0.250            | 0.03                                    | 0.97                                     | 0.84                                     | 0.61                                     |

**Table 3.** 95% CI for the probability of SAE

| Observed SAE (n=24) | 95% Confidence Interval |
|---------------------|-------------------------|
| 0/24                | 0.0 – 13.8%             |
| 1/24                | 0.7 – 20.2%             |
| 2/24                | 2.3 – 25.8%             |
| 3/24                | 4.3 – 31.0%             |
| 4/24                | 6.7 – 35.9%             |
| 5/24                | 9.2 – 40.5%             |

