### **11.2 Expected analyses and outcomes**

#### **11.2.1 Safety of MVA.HIVA**

Determined by comparing adverse events, reactogenicity, haematological and biochemical data from the MVA.HIVA recipients and controls. See Tables 2 and 3 for the probabilities of detecting events given the current trial design.

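### Table 2 (Protocol section 4.1) is labelled n=24 but contains the binomial probabilities for n=12, so the stated chances of seeing SAEs are wrong

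*Protocol*

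**What the plan says.** Section 4.1 sets the size: "A total of 48 mother-infant couples will be enrolled into the study and randomized in two groups of 24". It then introduces Table 2 as "the probabilities of observing 0, 1+ (1 or more), 2+ or 3+ SAEs among group of n=24", "for a range of possible true event rates". The caption reads "Probabilities of detecting events for n=24", and each of the four column heads also refers to 24 volunteers. The eight true rates run from 0.010 to 0.250.

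Table 3 follows, with 95% confidence intervals for 0 to 5 SAEs observed in 24 infants. The text takes from it an upper limit of 13.8% when no related SAE is seen.

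Section 11.1 says that no formal sample size calculation was done. Section 11.2.1, on the safety analysis, refers back to both tables: "See Tables 2 and 3 for the probabilities of detecting events given the current trial design".

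**The concern.** The two adjacent tables, both labelled n=24, do not fit together. At a true rate of 13.8%, the Table 3 upper limit for 0/24, the chance of no event in 24 infants is (1 − 0.138)^24 = 0.028. Table 2 prints a chance of no event of 0.14 at the higher rate of 15%. That chance must fall as the rate rises, so both cannot hold for 24 infants.

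Safety is a primary objective, and with no formal sample size calculation, Tables 2 and 3 are the only quantitative account of what 24 vaccinees can show about it. Someone who reads an SAE count against Table 2 would be misled. At a true rate of 10%, seeing no SAE would appear to be a 28% outcome when it is 8%, and three or more would appear to be an 11% outcome when it is 44%.

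**Working it through.** **Inputs, all from section 4.1:** group size n = 24; true rates p = 0.010, 0.025, 0.035, 0.050, 0.100, 0.150, 0.200, 0.250; tabulated quantities P(0), P(1+), P(2+), P(3+).

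**Formulas** (independent infants with a common rate p):

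- P(0) = (1−p)^n
- P(1+) = 1 − P(0)
- P(2+) = P(1+) − n·p·(1−p)^(n−1)
- P(3+) = P(2+) − [n(n−1)/2]·p²·(1−p)^(n−2)

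**One row in full, p = 0.050 (printed 0.54 / 0.46 / 0.12 / 0.02).**

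With n = 12:
- P(0) = 0.95^12 = 0.5404, so P(1+) = 0.4596
- P(2+) = 0.4596 − 12 × 0.05 × 0.95^11 = 0.4596 − 0.3413 = 0.118
- P(3+) = 0.118 − 66 × 0.0025 × 0.95^10 = 0.118 − 0.099 = 0.020 (0.0196 unrounded)

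This reproduces the printed row.

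With n = 24:
- P(0) = 0.95^24 = 0.292, so P(1+) = 0.708
- P(2+) = 0.708 − 24 × 0.05 × 0.95^23 = 0.708 − 0.369 = 0.339
- P(3+) = 0.339 − 276 × 0.0025 × 0.95^22 = 0.339 − 0.223 = 0.116

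No entry in the printed row agrees.

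**All rows, P(0) / P(1+) / P(2+) / P(3+):**

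| Rate | Printed | Exact, n=12 | Exact, n=24 |
|---|---|---|---|
| 0.010 | 0.88 / 0.11 / 0.01 / <0.01 | 0.8864 / 0.1136 / 0.0062 / 0.0002 | 0.7857 / 0.2143 / 0.0239 / 0.0017 |
| 0.025 | 0.74 / 0.26 / 0.03 / <0.01 | 0.7380 / 0.2620 / 0.0349 / 0.0029 | 0.5446 / 0.4554 / 0.1202 / 0.0214 |
| 0.035 | 0.65 / 0.35 / 0.06 / 0.01 | 0.6521 / 0.3479 / 0.0641 / 0.0074 | 0.4253 / 0.5747 / 0.2046 / 0.0502 |
| 0.050 | 0.54 / 0.46 / 0.12 / 0.02 | 0.5404 / 0.4596 / 0.1184 / 0.0196 | 0.2920 / 0.7080 / 0.3392 / 0.1159 |
| 0.100 | 0.28 / 0.72 / 0.34 / 0.11 | 0.2824 / 0.7176 / 0.3410 / 0.1109 | 0.0798 / 0.9202 / 0.7075 / 0.4357 |
| 0.150 | 0.14 / 0.86 / 0.56 / 0.26 | 0.1422 / 0.8578 / 0.5565 / 0.2642 | 0.0202 / 0.9798 / 0.8941 / 0.7202 |
| 0.200 | 0.07 / 0.93 / 0.73 / 0.44 | 0.0687 / 0.9313 / 0.7251 / 0.4417 | 0.0047 / 0.9953 / 0.9669 / 0.8855 |
| 0.250 | 0.03 / 0.97 / 0.84 / 0.61 | 0.0317 / 0.9683 / 0.8416 / 0.6093 | 0.0010 / 0.9990 / 0.9910 / 0.9602 |

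**Agreement.**
- At n=12, 31 of 32 cells agree to two decimals. The exception is P(0) at 0.010, exact 0.8864 and printed 0.88. It looks truncated, because 0.88 + 0.11 = 0.99 rather than 1. The largest difference is 0.006.
- At n=24, one cell agrees: P(3+) at 0.010, printed <0.01, exact 0.0017. The largest difference is 0.46, for P(3+) at 0.150 (printed 0.26, exact 0.72).
- Over all n from 8 to 30, no value other than 12 agrees in more than 6 cells.

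**Table 3.** The Wilson score interval at n=24 reproduces all six rows. For 0/24 the upper limit is z²/(n + z²) = 3.84/(24 + 3.84) = 13.8%, with z = 1.96. At n=12 the same formula would give 3.84/15.84 = 24.2%. Table 3 was therefore computed for the actual group size and Table 2 was not.

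**The case against.** The arithmetic is hard to dispute, so the case on the other side concerns how much it matters.

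- **The error is conservative.** It understates the chance of seeing SAEs, so nobody is led to think the trial more sensitive than it is.
- **The size does not rest on it.** Section 11.1 disclaims a formal calculation, and section 4.1 presents the table as examples and also gives a pilot-study rationale. Table 3 is a second statement about safety, and it is right for n=24.
- **No rule uses it.** The halting rule responds to any SUSAR, the safety monitor and DMEC act on individual events, and the safety analysis compares observed data between groups.
- **A few low-rate cells hardly move.** One is still correct. Two others differ by about 0.02 or less: P(2+) at 0.010, and P(3+) at 0.025.
- **The 13.8% is a Wilson limit.** It was not obtained by solving for P(0), so the clash between the tables is supporting evidence and the direct binomial check is the proof.

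All of this stands, and it limits the consequences: neither the sample size nor any decision rule needs to change. It does not make the table right. The protocol offers these figures as its safety sizing and relies on them in section 11.2.1 as properties of the current design. They belong to a group half that size, which appears nowhere in the document.

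**Conclusion.** The concern holds. Table 2 is a Binomial(12, p) table under an n=24 label, and 31 of its 32 cells are wrong for the trial as designed.

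The chance of at least one SAE is understated by 0.10 at a 1% rate (0.11 against 0.21), by 0.25 at 5% (0.46 against 0.71) and by 0.20 at 10% (0.72 against 0.92). The chance of seeing none is overstated by the same amounts, apart from the truncated cell at 1%. The largest single error is 0.46.

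The conclusion assumes only what any such table assumes: independent infants with a common SAE rate, and all 24 in Group 1 vaccinated. It needs no outside figure. The table must be corrected, because it misstates a design property on a primary objective; the design itself is unaffected.

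**What to change.** Replace the body of Table 2 with the exact binomial values for n=24:

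| Rate | 0 events | 1+ | 2+ | 3+ |
|---|---|---|---|---|
| 0.010 | 0.79 | 0.21 | 0.02 | <0.01 |
| 0.025 | 0.54 | 0.46 | 0.12 | 0.02 |
| 0.035 | 0.43 | 0.57 | 0.20 | 0.05 |
| 0.050 | 0.29 | 0.71 | 0.34 | 0.12 |
| 0.100 | 0.08 | 0.92 | 0.71 | 0.44 |
| 0.150 | 0.02 | 0.98 | 0.89 | 0.72 |
| 0.200 | <0.01 | >0.99 | 0.97 | 0.89 |
| 0.250 | <0.01 | >0.99 | 0.99 | 0.96 |

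The caption, column heads, Table 3 and the cross-reference in section 11.2.1 can stay as they are. The cost is a protocol correction to one table, with no change to sample size, conduct or analysis.

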**CONFIDENTIAL****4.2 Randomisation**

Infants who have been sensitised into the study will be invited to attend Sukuta Health Centre at 19 weeks of age. Those with a documented BCG vaccination within the first two weeks of life who have received all their EPI vaccines on schedule at the Sukuta Health Centre will be eligible for recruitment. Parents of those infants who meet all inclusion and none of the exclusion criteria will be asked to sign the informed consent form. A baseline blood sample will be taken and they will be asked to return to the Health Centre at 20 weeks of age. When they return for their 20 week visit the blood results will be checked and providing they still meet the inclusion and exclusion criteria they will be randomised to one of the two study groups of 24 (Table 4) by picking the next envelope (block randomised). The sensitisation number and allocation to vaccine group will be entered into the enrolment log. This will assign them to one of the two treatment groups: Group 1 will receive MVA.HIVA and Group 2 will not receive any vaccines. Infants recruited into this study will receive their routine EPI and study vaccines from the study team in order to reduce confounding variables that might result from variations in age at vaccination, and batch of vaccines administered.

**Table 4. Study groups**

| Group | n  | Treatment                              |
|-------|----|----------------------------------------|
| 1     | 24 | 5x10  pfu of MVA.HIVA i.m. |
| 2     | 24 | No vaccine (Control)                   |

**Masking**

It will not be a blinded study, however, the personnel who are performing the immunology assays (primary outcome measures) will be masked as they will be dealing with coded laboratory specimens and not know the allocation to groups.

**5 STUDY POPULATION**

All subjects must meet all of the inclusion criteria and none of the exclusion criteria to participate in this study.

**5.1 Inclusion Criteria**

- Healthy infants, 19 weeks of age, with weight for age z-scores within 2 standard deviations of normal.
- Have received all standard EPI immunizations according to national immunization programme (Table 5).
- Written informed consent by parent.
- Mother HIV-1/2-uninfected.

**Table 5.** Overview of EPI vaccination schedule in The Gambia in the first 12 months of life

**CONFIDENTIAL**

| Age   |                            |
|-------|----------------------------|
| Birth | BCG, OPV, HepB             |
| 8 w   | OPV, Pentavalent, PCV-7    |
| 12 w  | OPV, Pentavalent, PCV-7    |
| 16 w  | OPV, Pentavalent, PCV-7    |
| 9 m   | Measles, Yellow fever, OPV |

**5.2 Exclusion Criteria**

- a. Acute disease at the time of vaccination (acute disease is defined as the presence of a moderate or severe illness with or without fever). All vaccines can be administered to persons with a minor illness such as diarrhoea, mild upper respiratory tract infection with or without low-grade febrile illness, i.e. axillary temperature of  $<37.5^{\circ}\text{C}$  ).
- b. Axillary temperature of  $\geq 37.5^{\circ}\text{C}$  at the time of vaccination.
- c. Any clinically significant abnormal finding on screening from biochemistry or haematology at 19 weeks.
- d. History of allergic disease or reactions likely to be exacerbated by any component of the vaccine, e.g. egg products.
- e. Presence of any underlying disease that compromises the diagnosis and evaluation of response to the vaccine.
- f. Invasive bacterial infections (pneumonia, meningitis).
- g. Any other on-going chronic illness requiring hospital specialist supervision.
- h. Administration of immunoglobulins and/or any blood products within one month preceding the planned administration of the vaccine candidate.
- i. Any history of anaphylaxis in reaction to vaccination.
- j. Research physician's assessment of lack of willingness by parents to participate and comply with all requirements of the protocol, or identification of any factor felt to significantly increase the infant's risk of suffering an adverse outcome.
- k. Likelihood of travel away from the study area.
- l. Untreated malaria infection.
- m. Any other clinical evidence of infection.

**5.3 Sensitisation and Recruitment Procedures**

Field workers will approach women shortly after delivery at Sukuta Hospital and provide them with study information sheet in a language that they understand. Women will be encouraged to discuss the study with their husbands and involve the husband in the decision making process. The study information sheet will provide full details of the study procedures and what will be required of them if they participate. The information sheet will include: the purpose of the study and what it will involve for the infants will be described, including the study screening and the informed consent procedure, methods of vaccination, observation details, spectrum of likely side effects, possible adverse reactions, follow-up details and extent of blood sampling, as well as risks of vaccination and the unproven benefits of vaccination. The need for an HIV vaccine including a simple picture of the burden of HIV on the community, country and Africa, the current status of HIV-1 vaccine development including the fact that it is likely to be a prolonged process, will be explained. It will be stressed that this is an experimental vaccine and it cannot be guaranteed to provide protection. The need for a health screening before receiving vaccinations

## **CONFIDENTIAL**

because the vaccine is in an early stage of development will be explained. The information sheet will have been submitted to and will have received approval from the local ethics committee.

Parents must understand that these vaccines cannot cause HIV / AIDS.

Parents must understand that the MVA.HIVA vaccine has not been shown to prevent HIV infection and this will be stressed during the recruitment stage.

As it is an MRC policy, study parents are told that they cannot be a subject in a vaccine trial or any drug trial whilst they are a participant in this study.

Women, and their husbands if present who have been sensitised, will be invited to return for a screening visit when their child has reached 16 weeks of age. If they are still interested in participating in the study, they will be invited to ask questions, and when fully satisfied with all the answers will be asked to read and sign (or thumb-print) the informed consent document which will have been approved by the combined Gambian Government / MRC Joint Ethics Committee. Consent must be obtained prior to any study-related evaluations being performed (see consent check list, appendix). One copy of the signed consent form will be given to the parents, and a second copy will be retained by the investigator. Those infants whose parents have signed the consent document will be assessed at Sukuta health centre as described below in the study schedule.

It will be stressed that the infants can be withdrawn from the study at any stage.

## **6 STUDY ENROLMENT AND SCHEDULE OF FOLLOW-UP VISITS**

Infants who meet all inclusion and none of the exclusion criteria will be assigned a 3 digit study identification number (sensitisation number) if the parents have expressed an interest in the child participating in the study. They will retain this number for the duration of the study including at randomization. The consent form will need to be signed before the first study intervention at the 16 week visit (Visit 1). The randomisation into one of the treatment groups will be performed at their 20 week visit (Visit 3) (Table 6).

Infants recruited into this study will receive their routine EPI and study vaccines from the study team in order to reduce confounding variables that might result from variations in age at vaccination, and batch of vaccines administered.

All Gambian infants are issued with a blue health card at birth. A sticker indicating that the child is involved in an MRC study and should only receive EPI vaccines from the study team at Sukuta Health Centre up to the age of 9 months will be placed on the blue health card. This sticker will be removed when the child ceases to be in the study (i.e. end of the study period, not eligible for randomisation or dropped out). Table 6 illustrates the sequence of events from recruitment at birth, through to MVA.HIVA vaccination and the subsequent follow-up visits (explained in more detail in the text that follows):

**CONFIDENTIAL****Table 6.** Sequential events from delivery through vaccination & follow-up visits

| Age of study infants                                       | 16w | 19w   | 20w      | 21w   | 28w   | 36w                 |
|------------------------------------------------------------|-----|-------|----------|-------|-------|---------------------|
| Study visit                                                | 1   | 2     | 3        | 4     | 5     | 6                   |
| Bleeding schedule relative to study product administration |     | -1w   |          | +1w   | +8w   | +16w                |
| Group 1 (n=24)                                             | EPI | Bleed | MVA.HIVA | Bleed | Bleed | Bleed
EPI
ESP |
| Group 2 (n=24)                                             | EPI | Bleed |          | Bleed | Bleed | Bleed
EPI
ESP |

**Bleed** – 5 mL of blood; EPI = Vaccines of Expanded Programme on Immunization;  
**ESP** = End of study protocol; w = week

**6.1 Laboratory Tests**

**Haematology** Full blood count (FBC) including platelet count

**Biochemistry** Creatinine, alanine transaminase (ALT), alkaline phosphatase (ALP), bilirubin

**MVA.HIVA immunogenicity** Frequency of IFN- $\gamma$  producing cells using ex-vivo and cultured ELISPOT assays after overnight stimulation with pools of 15-mer peptides overlapping by 11 amino acids spanning the length of antigen HIVA.

**EPI immunogenicity** Measurement of vaccine-induced antibody levels to DTwP, Hib, HepB, PCV-7 and OPV.

**Table 7.** Temporal course of infant blood investigations

| Investigation           | Wk 19 | Wk 21 | Wk 28 | Wk 36 |
|-------------------------|-------|-------|-------|-------|
| Haematology             | X     | X     | X     |       |
| Biochemistry            | X     | X     | X     |       |
| MVA.HIVA Immunogenicity | X     | X     | X     | X     |
| EPI Immunogenicity      | X     | X     |       |       |
| HIV test                |       |       | X     |       |
| HLA typing              |       |       |       | X     |

